# A Smartphone App to Promote Healthy Weight Gain, Diet, and Physical Activity During Pregnancy (HealthyMoms): Protocol for a Randomized Controlled Trial

**DOI:** 10.2196/13011

**Published:** 2019-03-01

**Keywords:** telemedicine, pregnancy, gestational weight gain, diet, exercise, smartphone, mobile phone

## Abstract

**Background:**

Excessive gestational weight gain is common and associated with adverse outcomes both in the short and long term. Although traditional lifestyle-based interventions have shown to mitigate excess gestational weight gain, little is known about whether mobile Health (mHealth) apps can promote healthy weight gain, diet, and physical activity during pregnancy.

**Objective:**

The primary aim of the HealthyMoms trial is to determine the effectiveness of a smartphone app (HealthyMoms) for mitigating excess gestational weight gain during pregnancy. Secondary aims are to determine the effectiveness of the app on dietary habits, physical activity, body fatness, and glycemia during pregnancy.

**Methods:**

HealthyMoms is a two-arm randomized controlled trial. Women are being recruited at routine visits at the maternity clinics in Linköping, Norrköping and Motala, Sweden. Women are randomized to the control or intervention group (n=150 per group). All women will receive standard care, and women in the intervention group will also receive the HealthyMoms smartphone app.

**Results:**

Recruitment of participants to the trial was initiated in October 2017, and 190 women have so far completed the baseline measurement. The baseline measures are estimated to be finalized in December 2019, and the follow-up measures are estimated to be completed in June 2020.

**Conclusions:**

This project will evaluate a novel smartphone app intervention integrated with existing maternity health care. If successful, it has great potential to be implemented nationally in order to promote healthy weight gain and health behaviors during pregnancy.

**International Registered Report Identifier (IRRID):**

DERR1-10.2196/13011

## Introduction

### Background

Studies from developed countries including Sweden report that almost half of all pregnant women exceed the Institute of Medicine’s recommendations for gestational weight gain [1-3]. This is concerning because excess gestational weight gain is associated with negative outcomes for maternal and child health both in the short term (eg, gestational diabetes, preeclampsia, large for gestational age infants, and cesarean delivery) and long term (postpartum weight retention and obesity in the offspring) [1,2,4-6]. Thus, prevention of excess gestational weight gain is a public health priority. A 2015 Cochrane review concluded that diet, exercise, or both interventions reduced the risk of excess gestational weight gain by 20% [7]. These results are promising and suggest that lifestyle-based interventions can mitigate excess gestational weight gain during pregnancy. Notwithstanding these positive findings, previous studies have used traditional face-to-face education by means of individual or group counselling with heavy reliance on intensive support from clinical providers, which limits the scalability of these programs [7]. Considering the potential public health benefits, it is important to develop interventions that can reach a large proportion of the target group.

In the past 5-10 years, there has been a large increase in research on the use of mobile phones (including smartphones) for delivering behavior change interventions. The benefits of such mobile health (mHealth) programs are that they can be delivered anywhere at any time, they are interactive, and they can be tailored to meet people’s needs. Several reviews have concluded that mHealth programs may be effective for achieving changes in behavior and weight loss [8,9]; mHealth interventions may therefore also be effective in promoting a healthy lifestyle and gestational weight gain in pregnant women [10]. Additionally, mHealth offers a potential solution to provide support for pregnant women, in general, since mobile phones are commonly accessible, irrespective of socioeconomic status [10]. However, to date, mHealth interventions to promote healthy gestational weight gain in healthy pregnant women are scarce [11]. Therefore, further studies are warranted to determine the utility of mHealth for mitigating gestational weight gain during pregnancy.

### Aim

This paper reports the study design and methods of the HealthyMoms trial (trial registration: ClinicalTrials.gov NCT03298555). The primary aim of the HealthyMoms trial is to determine the effectiveness of a smartphone app (HealthyMoms) for mitigating excess gestational weight gain during pregnancy. Secondary aims are to determine the effectiveness of the app on dietary habits, physical activity, body fatness, and glycemia during pregnancy.

## Methods

### Study Design

The HealthyMoms trial is a two-arm parallel randomized controlled trial. The intervention group will receive standard care plus the HealthyMoms app (a 6-month program delivered through their smartphones). Participants in the control group will receive standard antenatal care provided by the maternity health care system. The study will be conducted and described according to the Standard Protocol Items: Recommendations for Interventional Trials 2013 statement [12] and the CONSORT-EHEALTH checklist [13]. The outline of the HealthyMoms trial is presented in Figure 1. The baseline measurements and randomization are conducted in gestational week 14, and the intervention will be initiated in gestational week 15. Measurements after the intervention will be conducted in gestational week 37.

### Eligibility and Recruitment

Eligible pregnant women are identified at the routine visits in the first trimester at the maternity clinics in Linköping, Norrköping, and Motala in Sweden. Inclusion criteria are a single pregnancy, age of 18 years or above, and ability to speak and read Swedish sufficiently well in order to understand the content of the HealthyMoms app and provide informed consent. Exclusion criteria are previously diagnosed eating disorder, pre-pregnancy diabetes, other medical conditions, or pharmacological treatments prior to pregnancy that may affect body weight.

### Randomization and Blinding

Following baseline measurement, participants will be randomly allocated to either the intervention or control group in a 1:1 ratio using restricted randomization (with a block size of 2) generated using STATA (version 13; StataCorp, College Station, TX) by a statistician. Opaque envelopes will be used for allocating participants to the respective groups, ensuring allocation concealment. Due to the nature of the intervention, participants will not be blinded to their allocation.

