### Sample Size and Power Considerations

Power for an independent *t* test was calculated *a priori* using G*Power 3.1 [20]. A total of 226 women (113 in each group) completing the measurements after the intervention provides 80% power (α=.05, two-sided), assuming a common SD in gestational weight gain of 4 kg [21] to detect a difference of 1.5 kg between the groups. Given our previous experiences [22], we anticipate that no more than 25% of the women will drop out of the study or have a child prematurely. Thus, we will recruit 300 women (150 in each group) to participate in the study.

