## Results

The HealthyMoms app was finalized in September 2017. Recruitment of participants to the trial was initiated in October 2017, and 190 women have so far completed the baseline measurement. The baseline measurements are estimated to be finalized in December 2019, whereas the follow-up of the mothers and infants is estimated to be completed in June 2020.

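### With a fixed block size of 2 and unblinded participants, opaque envelopes do not ensure allocation concealment: up to half of the allocations can be deduced

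*Protocol article*

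**What the plan says.** The protocol article, under Randomization and Blinding, has women "randomly allocated to either the intervention or control group in a 1:1 ratio", "using restricted randomization (with a block size of 2) generated using STATA". One block size is given, with no mention of varying sizes. The same section adds: "Opaque envelopes will be used for allocating participants to the respective groups, ensuring allocation concealment". It then says: "Due to the nature of the intervention, participants will not be blinded to their allocation". It does not say whether the staff who recruit, measure or open envelopes are blinded or kept unaware of the block size.

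On timing, Study Design states: "The baseline measurements and randomization are conducted in gestational week 14". Randomization and Blinding places allocation after the baseline measurement. The planned total is in Sample Size and Power Considerations: "Thus, we will recruit 300 women (150 in each group) to participate in the study". Recruitment was still open when the article appeared. According to Results, "190 women have so far completed the baseline measurement".

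**The concern.** Concealment means that nobody involved in enrolling a woman can foresee her arm. An opaque envelope hides the card inside it, but it cannot hide an allocation that follows from the one before. In a 1:1 block of two, the second place always goes to the arm that the first did not get. Participants know their arm, so the previous allocation can easily become known to those around the trial. The article thus gives a design feature that defeats concealment and, in the next sentence, claims that concealment is ensured.

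What is at stake is selection before allocation. Someone who foresees the arm could, without intending it, influence when a woman is scheduled, how warmly she is encouraged to enter, or how the week 14 weight is taken. That weight matters because the primary outcome (Gestational Weight Gain) is the week 37 weight minus the week 14 weight. The planned independent t test does not remove a prognostic difference created in this way. The adjusted regression is only to be considered, and its three dichotomised covariates would not capture, for example, motivation.

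**Working it through.** **Inputs from the protocol article.** Block size 2, ratio 1:1 (Randomization and Blinding); 300 women, 113 completers per arm, SD 4 kg, difference 1.5 kg, two-sided alpha 0.05 (Sample Size and Power Considerations); 190 women past baseline (Results).

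**The plan's own figure.** For an independent t test with 113 per arm, the noncentral t distribution gives a power of 0.801 (0.798 at 112 per arm), so 113 per arm reproduces. Allowing for 25% loss, 226 / 0.75 = 301.3, so 302 against the 300 stated; equivalently 300 × 0.75 = 225. The sample size is not affected by this point. It supplies the SD and group size used below.

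**Predictability.** The possible blocks are AB and BA. The first place is a 50:50 guess and the second is certain given the first.

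- Determined share: 1/2, so 300 × 1/2 = 150 allocations.
- Expected correct guesses: (0.5 + 1) / 2 = 75%, so 225 of 300, against 50% under simple randomisation.

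Enumerating all 1:1 permuted blocks, and guessing the arm with more places left, gives:

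| Block size (known to the guesser) | Determined | Correct guesses |
|---|---|---|
| 2 | 50.0% | 75.0% |
| 4 | 33.3% | 70.8% |
| 6 | 25.0% | 68.3% |
| 8 | 20.0% | 66.6% |

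A block of 2 is the most predictable permuted block that exists.

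**Exposure after publication.** 300 − 190 = 110 women remained, which is 110 / 2 = 55 determined allocations.

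**Illustration of bias.** The shifts are assumptions; the documents give no value. Let *g* be the difference between arms in expected weight gain, caused by selection, among second-slot women only, in every pair. About half of each arm sits in a second slot, so the overall bias is *g* / 2. The standard error of the difference is 4 × √(2/113) = 0.532 kg. With no true effect, the noncentrality is bias / 0.532, and the two-sided rejection rate comes from the t distribution with 224 degrees of freedom.

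| *g* (kg) | Bias (kg) | Noncentrality | Type I error |
|---|---|---|---|
| 0.5 | 0.25 | 0.47 | 7.5% |
| 1.0 | 0.50 | 0.94 | 15.5% |
| 1.5 | 0.75 | 1.41 | 28.9% |

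Here *g* is the contrast between the arms. A shift of 0.5 kg one way in second-slot app women together with 0.5 kg the other way in second-slot control women is *g* = 1.0, not 0.5.

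**The case against.** A reader might infer that every second allocation is known in advance and that concealment has failed outright. The documents do not support that. Deduction requires both the block size and the previous allocation in the same list. The article does not say who opens envelopes, what recruiters know, or whether there is one list or one per clinic, and a condensed article may leave such procedures to the full protocol. Only participants are stated to be unblinded; that staff are too is an inference.

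The opportunity is also narrower than the arithmetic alone suggests. Under Eligibility and Recruitment, women are identified at routine first-trimester visits, well before allocation, so a recruiter would have to foresee a woman's eventual place in the list. The Discussion says that every eligible woman is offered entry, which limits discretion over who is invited. Tying allocation to the week 14 visit leaves little room to reorder women. Differential encouragement to stay in the trial after allocation would arise under any block size and does not belong to this point.

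These limits stand. They reduce the likely size of any bias, but they leave scheduling, encouragement to enter and the week 14 weight as possible routes. They do not rescue the claim that envelopes ensure concealment. Keeping the block size secret would have been a partial defence, but publication during recruitment removes it for the women still to come.

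**Conclusion.** The concealment claim is wrong as written: concealment is not ensured. Up to 150 of 300 allocations (50%) can be deduced, about 55 of them among the 110 women still to be randomised at publication. The 50% and 75% figures are ceilings that apply to someone who knows the block size and sees each previous allocation in the list.

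It would go too far to conclude that selection bias occurred or that the trial's result is biased by a particular amount. The bias figures rest on assumed shifts exploited in every predictable pair, on the plan's SD of 4 kg, and on 113 completers per arm with loss unrelated to position in the block. They show that a modest contrast would matter against a 1.5 kg target, not that one exists.

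**What to change.** 1. For women not yet randomised, discard the rest of the block-of-2 list. The statistician should issue a new one, either by simple randomisation or with randomly varying larger blocks. Block sizes should be withheld from recruiting and measuring staff and not published until recruitment ends. Withholding matters: by the table above, larger blocks of known size still allow about 67% to 71% correct guesses.
2. Replace the concealment claim with a statement that envelopes hid the card but that allocations could be predicted under blocks of 2. Say who knew the block size and earlier allocations.
3. For women already randomised, compare baseline weight, BMI, parity and education between arms within second-in-block positions, as a check for selection. Agreement would reassure but could not exclude selection on unmeasured traits such as motivation.

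**Cost.** A new list and new envelopes. With simple randomisation of 110 women, the difference in group sizes has an SD of √110 ≈ 10.5 women, and the variance rises by about 110 / 300² ≈ 0.1%.

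**Limit.** The change reaches at most 110 / 300 = 37% of the sample, and fewer if more women have been randomised since the count of 190. If the 0.5 kg bias applied throughout, it would remove about 0.5 × 110 / 300 = 0.18 kg. It cannot protect women already randomised.

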**Figure 1 figure1:**
[figure not shown]
Study design of the HealthyMoms trial.

### Intervention

#### Overall

The HealthyMoms app is a comprehensive 6-month program aimed at mitigating excess gestational weight gain by promoting a healthy diet and physical activity. A screenshot of the HealthyMoms app is shown in Figure 2. The app is Android and IOS compatible. Participants who are allocated to the intervention group will receive a text message with a link to a website, which they can access through their phone. Using the website, participants will be instructed to register and download the app from Google Play or App Store.

#### Development

The HealthyMoms app utilizes the same platform (ScientificMed Tech AB) [14] and structure as our previously validated app targeting parents with preschool aged children [15]. The specific content and features for the HealthyMoms app were developed by a multidisciplinary team with expertise in nutrition, behavioral science, obstetrics, psychology, physiotherapy, and physical activity. Intervention development was an iterative process, whereby input from target group members and experts as well as behavior change theory (social cognitive theory [16] and behavior change techniques [17]) were considered. Specifically, input on the content and features were discussed in semistructured interviews with pregnant women and women who had recently given birth (n=10). Further, content regarding maternal and fetal development as well as dietary recommendations were reviewed by midwives and relevant experts at the National Food Agency, Sweden. Theory was used to inform the development of the intervention. For example, key behavior change techniques such as shaping knowledge (eg, general information on healthy diet, physical activity, and gestational weight gain), goals and planning (eg, goal setting and identification of barriers), and feedback and monitoring (eg, self-monitoring of behavior and feedback on behavior).

#### Content and Use

The HealthyMoms app delivers a comprehensive program of information and push notifications based on evidence-based recommendations for a healthy diet [18], physical activity [19], and weight gain [1] in pregnant women. The app consists of seven features: weekly themes; push notifications; self-monitoring and feedback features of gestational weight gain, diet, and physical activity; recipe feature; exercise feature; pregnancy calendar; and app library (eg, frequently asked questions and practical tips).

The program addresses 12 *themes* that change every other week: healthy foods, healthy weight gain during pregnancy, physical activity and exercise during pregnancy, how to change a habit, cravings, fruits and vegetables, nutrition for the mother and baby, the third trimester, the reasons why we eat, exercise at the end of pregnancy, how to keep a new habit, and the time after the delivery. Participants are alerted when a new theme is initiated via a *push notification* every other week. In total, participants receive eight push notifications for every theme (one message every other day and an additional message). These messages consist of, for example, factual information or behavior change guidance, support and guidance on healthy habits (eg, diet and physical activity), weight gain during pregnancy, strategies for behavior change, encouragement, key messages, and reminders.

**Figure 2 figure2:**
[figure not shown]
Screenshot of the HealthyMoms app.

The app includes a *self-monitoring and feedback feature*, whereby diet, physical activity, and weight gain are reported by the user, which is followed by tailored feedback in the form of graphical illustration and text. Self-monitoring of diet involves answering five questions each week on the intake of fruits, vegetables, sweets, and sugary drinks. Participants receive feedback presented in a graph and in text with a “traffic light” (green: reached the recommendation, yellow: almost reached the recommendation, red: far from reaching the recommendation). Self-monitoring of physical activity entails setting a physical activity goal (in activity minutes) and reporting of weekly activity levels. Individual self-monitoring data are summarized graphically, and participants can see if they are close to or if they have met their own goal as well as the recommendation for physical activity (150 minutes/week) each week [19]. The participants also receive feedback in text format and with the “traffic light,” as described above. Self-monitoring of weight consists of reporting current weight. The weight gain is presented graphically; from gestational week 22 until the end of pregnancy, a green field is visible, showing the participant’s weight gain in relation to their individual recommended gestational weight gain (in accordance with the Institute of Medicine recommendation and calculated from their pre-pregnancy body mass index).

The app also includes an *exercise feature* and *a recipe feature*. The exercise feature includes information, tips, and exercise programs for the different stages of pregnancy in both text and video format. The recipe feature has a library of healthy recipes and weekly menus. The HealthyMoms app also includes a *pregnancy calendar* that is updated every week. It consists of information on fetal and maternal development during pregnancy as well as texts to the partner (eg practical information, encouraging, and supportive texts). Lastly, the app includes a *library* of practical tips, frequently asked questions, and useful links.

### Sample Size and Power Considerations

Power for an independent *t* test was calculated *a priori* using G*Power 3.1 [20]. A total of 226 women (113 in each group) completing the measurements after the intervention provides 80% power (α=.05, two-sided), assuming a common SD in gestational weight gain of 4 kg [21] to detect a difference of 1.5 kg between the groups. Given our previous experiences [22], we anticipate that no more than 25% of the women will drop out of the study or have a child prematurely. Thus, we will recruit 300 women (150 in each group) to participate in the study.

### Primary outcome

#### Gestational Weight Gain

The primary outcome gestational weight gain is calculated as the measured body weight in gestational week 37 minus the measured body weight in gestational week 14. Body weight is recorded using standardized procedures when the participant is wearing only underwear. We will also analyze gestational weight gain as within or above the Institute of Medicine-recommended levels by using the recommended weekly gains in body weight during the second and third trimester [1].

### Secondary Outcomes

#### Dietary Intake

Dietary intake is measured using Riksmaten FLEX [23], adapted to pregnant women. It combines three 24-hour recalls and a food-frequency questionnaire to measure intakes of foods and drinks. Intakes of energy, macronutrients, and micronutrients are calculated through linkage with the amount of foods assessed through Riksmaten FLEX to the food composition database of the National Food Agency of Sweden [24].

#### Physical Activity and Sedentary Behavior

Physical activity and sedentary behavior are measured objectively over seven consecutive 24-hour periods with a wrist-worn triaxial accelerometer, Actigraph wGT3x-BT (ActiGraph, Pensacola, FL). Wrist-worn accelerometers including the ActiGraph [25] have been validated previously in adults [25,26] and pregnant women [27]. The recorded movements will be processed as previously described [27,28] and converted to time spent on different activity levels (ie, sedentary behavior as well as light, moderate, and vigorous physical activity) using appropriate cutoffs.

#### Body Fatness

Body fatness is measured using Bod Pod (COSMED, Rome, Italy), as previously described [29]. This method utilizes air-displacement plethysmography to measure body volume. Body density is then calculated using the measured body volume and body weight. Subsequently, body fatness is calculated using the gestational-age specific densities for fat-free mass published by Van Raij et al [30]. These values from fat-free mass density have previously been shown to be suitable for use throughout pregnancy [31-33].

